## Assignment of interventions: blinding

### Who will be blinded {17a}

Due to the nature of the intervention, this study is an open-label trial to all participants and care providers. However, in order to reduce the level of bias, the statisticians involved in the data analysis will be blinded to the group allocation.

### Procedure for unblinding if needed {17b}

This is not applicable. The trial is a non-blinded trial.

## Data collection and management

### Plans for assessment and collection of outcomes {18a}

Data collection will be mainly conducted at T0, T1, and T2. Table 2 shows the complete outcome measures and their collecting methods. The details are described in the following sections.

**Table 2 Tab2:** The complete outcome measures and their collecting methods

Outcome measure		Collecting method
Systolic blood pressure		Clinic BP measurement
Diastolic blood pressure		Clinic BP measurement
Biochemical indexes	Blood urea nitrogen (BUN)	Laboratory test (blood test)
	Creatinine (Cr)	Laboratory test (blood test)
	Alanine transaminase (ALT)	Laboratory test (blood test)
	Aspartate transaminase (AST)	Laboratory test (blood test)
	Uric acid (UA)	Laboratory test (blood test)
	Low-density lipoprotein (LDL)	Laboratory test (blood test)
	High-density lipoprotein (HDL)	Laboratory test (blood test)
	Blood glucose (BG)	Laboratory test (blood test)
	Total cholesterol (TC)	Laboratory test (blood test)
	Triglyceride (TG)	Laboratory test (blood test)
Lifestyles	Obesity (BMI and WHR)	Basic body measurement
	Physical activity	Questionnaire (IPAQ)
	Diet (24-h urine sodium and potassium)	Laboratory test (24-h urine test)
Self-management adherence	Medication adherence	Questionnaire (HB-MAS)
	Self-monitoring adherence	System log
Hypertension awareness		Questionnaire (HK-LS)
Work efficiency of care providers	Frequency of follow-up in a day	System log
	Handling time for a follow-up request	System log

#### Blood pressure

Blood pressure (BP) measurement can be categorized into 2 types: clinic and out-of-office BP measurement [16]. Clinic BP measurement is performed by GPs or CMs under standard conditions and unified guidelines. Out-of-office BP measurement includes ambulatory BP monitoring and home BP monitoring, which can provide large amount of BP data outside the medical environment [30, 31]. In this trial, we will use clinic BP measurement to assess the variation in SBP and DBP from baseline to 12 months and use out-of-office BP measurement (home BP monitoring) to promote interventions in daily management. When performing clinic BP measurement, patients should be seated for at least 5 min in a quiet room before measurements and keep the upper arm at the heart level. Measurements will be conducted at least 2 times and taken 1–2 min apart. An additional measurement will be required in case that the first two readings differ by > 5 mmHg. The mean value of these readings will be recorded.

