**Fig. 1 Fig1:**
[figure not shown]
Diagram of PEICM

The 9 tasks can be grouped into 3 parts: the tasks for regular management, the tasks for pathway variation, and the tasks for self-management. The tasks for regular management include 4 tasks: diagnosis, risk assessment, hierarchical management, and regular follow-up. When a patient is diagnosed with hypertension, he/she will enter the pathway. A cardiovascular risk assessment will firstly be conducted to divide patients into 2 management levels: level 1 for patients in low or middle risk while level 2 for patients in high risk. The management plan for level 1 and level 2 is different. In addition, patients’ risk will be reassessed per week based on their self-monitoring data to dynamically change their management levels. Care providers need to perform regular follow-ups for patients, and the follow-up schedule will also be dynamically adjusted based on the management level. Once a patient is in level 2 for over 3 weeks, a two-way referral channel will be opened. The tasks for pathway variation include 2 tasks: abnormal condition intervention and compliance management. When patients’ self-monitoring data is abnormal, care providers will immediately be informed and conduct the appropriate intervention; when patients’ compliance is low, care providers need to perform an extra follow-up to learn the reason for low compliance and try to improve it. The tasks for self-management include 3 tasks: medication guidance, lifestyle guidance, and health education. Medication guidance aims to provide plans about drug prescription while lifestyle guidance aims to provide plans mainly for diet and physical activity. Health education aims to offer health knowledge to patients, in order to improve their hypertension awareness thus improving their self-management ability.

According to the pathway, the responsibility of each role is specified as follows: physicians are responsible for diagnosis and formulating the self-management plans; GPs are responsible for regular follow-ups, plan adjustment, and abnormal condition intervention; CMs are responsible for health education and compliance management. Patients need to follow self-management plans and perform self-monitoring to receive timely intervention from care providers.

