Based on PEICM, a telehealth system has been implemented, which consists of 2 parts: clients for care providers and patients, and a service engine for data storage and pathway execution (Fig. 2). For care providers, the client is in the form of a website that can be accessed on their computers in the hospital. Care providers use the client to supervise patients and conduct the intervention. For patients, the client is in the form of an all-in-one health terminal. The terminal is a combination of an Android tablet with a series of wearable devices (integrating measurement of ECG, heart rate, blood pressure, blood glucose, blood oxygen saturation, and body temperature), which was developed by ZICT (Shenzhen, China). Data measured by the terminal will be automatically uploaded and displayed on the website. In addition, patients can use the tablet to check their self-management plans, read health knowledge, and communicate with care providers. The functional design of the tablet application drew on experience from our previous work [28]. The service engine is a web service deployed on the server, consisting of 4 layers: a data layer, a service layer, a control layer, and an interface layer. The engine will be responsible for saving data from clients and providing decision support based on the pathway.

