### Outcomes {12}

The primary outcome of the trial is changes in mean systolic blood pressure (SBP) from baseline (T0) to 12 months (T2). The key secondary outcomes are changes in mean diastolic blood pressure (DBP) and changes in biochemical indexes related to hypertension from T0 to T2. The other secondary outcomes include changes in lifestyles, self-management adherence, and hypertension awareness from T0 to T1 (6 months) and T2. In addition, work efficiency of care providers will be assessed at T2 to validate the model from a care provider perspective.

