### Implementation {16c}

All patients who give written consent for participation will be enrolled. CMs will guide the enrolment session. First, each patient will be directed to the baseline assessment, including demographics, basic body measurement, clinical BP measurement, laboratory test, and questionnaires. Then, each patient will be randomly assigned an envelope, inside which is a printed random number with the corresponding group. CMs will open the envelope and find the treatment condition to be conducted for this patient. CMs then give the information about treatment allocation to the patient. After that, each group will be guided to different rooms, and CMs will instruct the use of the system to the control group and intervention group, respectively.

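### Clinic SBP, the primary outcome, is read by unblinded care-provider roles, so any arm-dependent reading bias at 12 months passes in full into the treatment comparison

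*Protocol article*

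**What the plan says.** Outcomes {12} makes the change in systolic pressure from baseline (T0) to 12 months (T2) the primary outcome. The Blood pressure section says which measurement counts: "we will use clinic BP measurement to assess the variation in SBP and DBP from baseline to 12 months". Table 2 agrees. Home monitoring is used to drive daily management.

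The same section says who measures: "Clinic BP measurement is performed by GPs or CMs under standard conditions and unified guidelines". On the number of readings it says: "Measurements will be conducted at least 2 times". A further reading is required when the first two differ by more than 5 mmHg, and the mean is recorded. Seated rest, arm position and spacing of readings are specified.

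These roles also deliver the care. Under Intervention description {11a}, "GPs are responsible for regular follow-ups, plan adjustment, and abnormal condition intervention", while CMs handle education and compliance. Table 1 has GPs conducting follow-up in the control group too. Under Implementation {16c}, "CMs will open the envelope and find the treatment condition to be conducted for this patient"; the baseline assessment, including clinic pressure, comes before that step.

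Who will be blinded {17a} describes the trial as open-label for participants and care providers, and adds as the one safeguard that "the statisticians involved in the data analysis will be blinded to the group allocation".

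**The concern.** The section on blinding attributes the open-label design to the nature of the intervention. That explains why patients and treating staff know the arm. It does not explain why the person taking the outcome reading should know it.

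A blood pressure reading can be influenced by how the visit is conducted, how a value is read or rounded, and whether another reading is taken. If the assessor knows the arm, these influences can differ between arms. The resulting error is systematic, so a larger sample does not average it out, and a blinded statistician receives data that already contain it.

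The Discussion acknowledges the open-label design. The biases it names are poor compliance or dropout among control patients, and providers departing from the guidelines for controls. It does not mention biased measurement of the outcome. The trial's main conclusion rests on this one reading.

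**Working it through.** **Inputs from the protocol article.** Sample size {14}: difference 5 mmHg, SD 16.5 mmHg, α 5%, power 0.80, 171 per group at the end of the trial. Statistical methods {20a}: two-sided 5% tests. Trial design {8}: 1:1 allocation.

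**Step 1. Reproduce the plan's figure.** n per group = 2 × (1.960 + 0.842)² × 16.5² / 5² ≈ 171, or 342 in total, as stated. Power at 171 per group is 0.800. The sample size is sound.

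**Step 2. Where bias can enter.** Let b be the arm-dependent reading bias at a visit, intervention minus control. At T0 the envelope is still closed, so b(T0) = 0 as far as allocation is concerned. The bias in the between-arm difference in change is therefore b(T2) − b(T0) = b(T2), with no cancellation.

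**Step 3. Precision.** SE = 16.5 × √(2/171) = 1.784 mmHg. A difference of 1.96 × 1.784 ≈ 3.5 mmHg is significant.

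**Step 4. False-positive rate with no true effect.** The documents give no bias size; 0 to 3 mmHg is an assumed range, with b taken as its magnitude in favor of the intervention. Rate = P(Z > 1.96 − b/1.784) + P(Z < −1.96 − b/1.784).

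| Assumed b (mmHg) | Two-sided rate | Part favoring the intervention |
|---|---|---|
| 0 | 5.0% | 2.5% |
| 1 | 8.7% | 8.1% |
| 2 | 20.2% | 20.1% |
| 3 | 39.0% | 39.0% |

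With 201 per group (402 enrolled, none lost), SE = 16.5 × √(2/201) = 1.646 mmHg, and biases of 1, 2 and 3 mmHg give about 9%, 23% and 45%. More patients make a fixed bias more likely to reach significance.

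**Step 5. Inflation of a real effect, 171 per group.** With a true effect of 3 mmHg, a bias of 2 mmHg raises the chance of a significant result from 39% to 80%. With a true effect of 5 mmHg, a bias of 1 mmHg raises it from 80% to 92%.

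**Step 6. Contribution of the reading count alone.** This was simulated with an assumed within-visit SD of 3, 5 or 7 mmHg. In one arm only, up to one, two or three optional readings were added while the running mean stayed above the patient's usual level. The recorded mean fell by about 0.26 to 0.50 mmHg (SD 3), 0.38 to 0.76 (SD 5) or 0.50 to 1.00 (SD 7). Even with deliberate use in one arm, this stays at or below about 1 mmHg.

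**The case against.** **The sentence on who measures belongs to a general description of blood pressure types.** It does stand before the trial-specific text. But the same paragraph and Table 2 make clinic pressure the trial's outcome, no other assessor is described, and CMs guide the enrolment session at which baseline pressure is taken. The objection does not remove the point. It does limit it: a reader might infer that each patient is measured by his or her own provider, and the documents do not say so.

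**Measurement is standardized and data are checked.** Rest, arm position, spacing and a trigger for a further reading are laid down. There is double data entry with range checks, and a quarterly audit. These reduce random error and transcription error. They do not hide the arm from the person measuring.

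**The device may be automatic.** This stands as a limit. Of the patient terminal the article says "Data measured by the terminal will be automatically uploaded and displayed on the website", and a reader might infer that clinic readings are manual and that automatic upload is kept for home use. The clinic device is not named, so that inference has no support. Automation would reduce reading error, but it would not govern optional extra readings or the conduct of the visit.

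**The reading rule is not really open-ended.** Its natural reading is two readings, or three when triggered. The triggered reading is neutral if applied alike in both arms. Only the absence of a maximum remains, and Step 6 shows that it is a minor contributor.

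**The bias is hypothetical.** Correct. A bias of 3 mmHg would be 60% of the 5 mmHg design effect, which is not small; 1 to 2 mmHg would be 20% to 40% of it.

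**Conclusion.** The point holds as a weakness of design. The primary outcome is assigned to roles that know the allocation and deliver care, and the only stated blinding acts after the data exist. A bias of 1 mmHg, well below the roughly 3.5 mmHg needed for significance, would lift the false-positive rate to about 9%; 2 mmHg would lift it to about 20%.

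These figures rest on the protocol's SD of 16.5 mmHg, 171 per arm, a normal approximation, and a bias size that is assumed throughout. They show that observer bias could create or inflate an effect. A reader might go further and infer that the result will be biased, or that baseline is compromised too. The documents support neither: they give no evidence on the size of any bias, and baseline is read before allocation is known.

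The unblinded assessor is the main issue, and the missing maximum on readings is secondary. The change is worth making because it is cheap and protects the main conclusion.

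**What to change.** 1. **Assessor.** At T1 and T2, roster the existing GPs or CMs at the health management center so that the person measuring does not manage that patient and is not told the arm. Ask patients not to disclose it. Outcome measurement is already at this one site and the staff come from three community centers, so no new staff should be needed. The article does not describe how patients are assigned to providers, so the roster must be checked against that.
2. **Reading rule.** Take exactly two readings, add a third only when the stated 5 mmHg rule is met, and average them. A tighter rule that applies equally to both arms does not bias the comparison.
3. **Device.** Use an automatic device that stores or uploads its readings, provided this is consistent with the device used at T0. Enrolment began in July 2020, so a change of method between T0 and T2 should be avoided.
4. **Supportive analysis (optional).** Mean home SBP in a fixed window around T2 may be added as supportive only. State the caveat that its completeness and selection may differ by arm, because compliance management and patient management plans run only in the intervention group, and that patients know their arm.

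**Cost.** Some scheduling effort at two visits. Masking may be incomplete because patients can reveal their arm. Since allocation can bias only T1 and T2, the change remains useful after enrolment has started.

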#### Biochemical indexes

Biochemical indexes are collected from the blood test, as shown in Table 2. These indexes are associated with cardiovascular risk factors, target organ damage, and the corresponding clinical conditions [32], which can indirectly reflect the control of hypertension.

#### Lifestyles

Lifestyle measure contains 3 parts: obesity, physical activity, and diet. Obesity is estimated by body mass index (BMI) and waist-to-hip ratio (WHR, for abdominal obesity), which will be measured in the basic body measurement. Physical activity will be assessed by the short form of International Physical Activity Questionnaire (IPAQ) [33]. Diet is evaluated by the intake of salt. Low-sodium diets will be assessed by the 24-h urine sodium collected from the 24-h urine test. The 24-h measurement of salt excretion in urine has proved to be the best method to measure salt intake [34]. Twenty-four-hour urine potassium will also be considered since increasing potassium intake properly in the diet can help reduce BP [35].

#### Self-management adherence

Adherence to self-management consists of 2 parts: medication adherence and self-monitoring adherence. Medication adherence will be assessed by the Hill-Bone Medication Adherence Scale (HB-MAS) including 9 items [36]. Self-monitoring adherence estimates the compliance with non-pharmacological treatment, which will be assessed by the system log data. We calculate the adherence based on the ratio of actual frequency of BP measurements to the number required by the management plan. The concrete formula can be found in our previous paper [28].

#### Hypertension awareness

Patients’ hypertension awareness reflects their self-management ability, which will be assessed by the Hypertension Knowledge-Level Scale (HK-LS) [37]. HK-LS contains 22 items with 6 sub-dimensions: definition, medical treatment, drug compliance, lifestyle, diet, and complication.

#### Work efficiency of care providers

Work efficiency of care providers will be calculated based on the follow-up data. In this trial, all the follow-ups are generated, conducted, and recorded through the system. The generated follow-up requests can be divided into 3 types: regular follow-up, abnormal attention follow-up, and compliance follow-up. The system needs to schedule all the follow-ups reasonably to make care providers handle requests timely. We propose 2 indexes to assess the work efficiency: one is the frequency of follow-up in a day, which demonstrates how our system reduces the time cost of a single follow-up; another one is the handling time of a follow-up request, which means the time duration before a generated follow-up request is handled. Intuitively, the more follow-up care providers conduct in a day and the less handling time a follow-up request costs, the more effective their work will be. We will derivate the average work efficiency of care providers in the entire trial period for the control group and the intervention group, respectively. For the handling time of a follow-up request, we will calculate time cost for the 3 types of follow-ups respectively, then sum it together with different weights to get the average time cost.

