### Sample size {14}

The power calculation is based on the primary outcome measure and aims for a mean systolic blood pressure variation of 5 mmHg with a standard deviation of 16.5 mmHg (the effect size is based on a previous study [29]). Assuming an α of 5%, and power of 0.80, 171 patients per group are required at the end of the trial (342 in total). Considering an attrition percentage of 15%, our aim is to include a minimum of 402 patients at baseline.

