## Discussion

This protocol has been designed to understand the effectiveness of a pathway-driveneHealth-based integrated care model, implemented as a full-featured telehealth system. Compared with prior studies [38, 39], our study innovatively introduces the concept of pathway, then combines it with information technology and the “three-manager” mode to establish a standardized and executable care model. Besides testing efficacy of the model, this study will have several other strengths if successful. First, the model can be generalized to other common chronic diseases, such as diabetes, stroke, and chronic obstructive pulmonary disease (COPD). The task-based pathway can be applied in both single disease and multiple chronic conditions. Second, the study would provide the feasibility evidence of the “three-manager” mode combined with information technology in China. Policy makers in other regions across the country could roll out similar services for better management. Last, the awareness, treatment, and control rates of hypertension in Sichuan, Yunnan, and Guizhou are relatively low compared with other provinces [40]. Therefore, performing such a trial in Yibin is significant to improve the local outcome for hypertension management.

The present protocol is also subject to some limitations. First, since the clients for patients are different from traditional mobile applications, participants may show different levels of acceptance in the system. Low system acceptance will lead to undesirable high attrition rates. We will adopt several strategies to improve patients’ acceptance of the system, including ongoing system updates with usability tests, online system guidance from CMs, and regular offline training sessions for patients. Second, this is an open-label trial for both patients and care providers. Patients in the control group may not comply with self-management regimes or even choose to discontinue the participation, and care providers may tend to conduct the management for the control group not following the guidelines. We plan to eliminate these potential biases through intensive training of care providers and reward mechanism on patients (for example, free outpatient registration), as well as supervision of intervention quality from the steering committee.

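### Average handling time has no value for follow-up requests that are never handled, so it is conditional on handling and leaves neglect unpenalised

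*Protocol article*

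**What the plan says.** The section Work efficiency of care providers, under {18a}, sets out two indexes taken from the system log. The first: "one is the frequency of follow-up in a day". The second: "another one is the handling time of a follow-up request, which means the time duration before a generated follow-up request is handled". The direction of the second is fixed: "the less handling time a follow-up request costs, the more effective their work will be". So is the summary: "We will derivate the average work efficiency of care providers in the entire trial period for the control group and the intervention group, respectively". Requests are of three types (regular, abnormal attention and compliance), and for handling time "we will calculate time cost for the 3 types of follow-ups respectively, then sum it together with different weights". The source is complete in principle, since "all the follow-ups are generated, conducted, and recorded through the system".

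Two other statements bear on whether some requests may stay open. Sample size {14} says: "Considering an attrition percentage of 15%, our aim is to include a minimum of 402 patients at baseline". The Discussion, on the open-label design, warns that "care providers may tend to conduct the management for the control group not following the guidelines".

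**The concern.** The measure is a duration that ends when a request is handled. If the request is never handled, the duration has no end and the average has no entry for it. Anyone who follows the text literally will average over handled requests only.

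That conditions an efficiency measure on the work having been done. An arm that leaves requests open pays no penalty in this index. If the requests it leaves open are the slow ones, its mean is shortened. Because shorter counts as better, the measure could then favour the arm that served its patients less well. The problem arises within each follow-up type, including the regular follow-ups that both arms receive, so it is separate from the choice of weights across types.

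**Working it through.** **1. Does another section bring unhandled requests back in?**

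- Missing data {20c} applies multiple imputation to incomplete assessments. An open request in a log is not an assessment.
- Retention {18b} says the log data of some patients will be explored. It covers only patients who discontinue before the 6-month evaluation and attend no assessment, and it gives no scoring rule. Later dropouts and requests skipped by providers fall outside it.
- The follow-ups-per-day index falls when requests are skipped, but it has no denominator of generated requests and cannot show the share left unhandled. Table 1 also gives abnormal-condition and compliance work to the intervention arm only, so the daily counts are not like for like.

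None of these supplies a value.

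**2. How much could attrition contribute?**

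The protocol states no handling-time figure, so there is none to reproduce. Its attrition figure gives 402 × 0.15 = 60.3, about 60 patients. The unit here is the request, however. Table 1 sets regular follow-up between once every 3 months (about 4 a year) and, at the most frequent, once every 2 weeks (about 26 a year):

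- 402 × 4 = 1,608 requests; 60 / 1,608 = 3.7%
- 402 × 26 = 10,452 requests; 60 / 10,452 = 0.6%

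If each dropout leaves one open request (an assumption), attrition touches roughly 0.6% to 4% of regular requests. Nothing in the document says these would be the slow ones.

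**3. Illustration A: slow requests abandoned after a cut-off (all inputs assumed).**

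Arm A has exponential handling times with mean 3.0 days and handles everything. Arm B has exponential times with mean m = 5.0 days, and requests still open at cut-off k are never handled. The unhandled share is q = exp(−k/m). The handled-only mean is m − k·q/(1 − q). For k = 7: q = exp(−1.4) = 0.247, and 5 − 7 × 0.247/0.753 = 2.7. Counting each unhandled request as 14 days gives 2.7 × 0.753 + 14 × 0.247 = 5.5.

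| Cut-off in B (days) | Unhandled in B | B, handled only | B, unhandled counted as 14 days | A |
|---|---|---|---|---|
| 14 | 6% | 4.1 | 4.7 | 3.0 |
| 7 | 25% | 2.7 | 5.5 | 3.0 |
| 5 | 37% | 2.1 | 6.5 | 3.0 |

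At 6% unhandled, B's mean is too short but the ranking is still right. At 25% and 37% the slower arm is ranked faster. Keeping the unhandled requests restores the order.

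**4. Illustration B: a difficult fraction p (all inputs assumed).**

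Ordinary requests average 2 days in both arms. One arm never handles the difficult fraction; the other handles it late, with mean 10 days. The handled-only means are 2.0 and 2(1 − p) + 10p. The 14-day restricted means use 2(1 − exp(−7)) = 2.0 for ordinary requests, 10(1 − exp(−1.4)) = 7.5 for late ones and 14 for those never handled.

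| p | Handled only: never vs late | Restricted mean: never vs late |
|---|---|---|
| 5% | 2.0 vs 2.4 | 2.6 vs 2.3 |
| 10% | 2.0 vs 2.8 | 3.2 vs 2.6 |
| 20% | 2.0 vs 3.6 | 4.4 vs 3.1 |
| 30% | 2.0 vs 4.4 | 5.6 vs 3.7 |

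The reversal in every row follows from the set-up, because exactly the slow requests are the ones dropped. The table shows what can happen, not what is likely.

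**5. Random skipping.**

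If 30% of requests in an arm with mean 3.0 days are skipped regardless of how long they would have waited, the handled-only mean stays at 3.0. The neglect is invisible, but it is not rewarded.

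**The case against.** The strongest reply is that the text never says open requests are dropped. Its unit is a generated request, its wording is compatible with a time-to-event analysis, and an analysis plan not shown could add censoring. That stands in part: exclusion is implied, not stated. But the article goes beyond naming the outcome. It fixes the definition, the direction and the averaging, and an average of these durations cannot take in a request without one.

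Second, a reader might infer that the neglecting arm will look faster. The documents do not support that. It requires the dropped requests to be the slow ones, and to be numerous enough; random skipping does not do it.

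Third, a reader might take the protocol to predict many unhandled requests. It does not. Step 2 puts the attrition path at a few per cent of regular requests at most. The Discussion warns of departure from guidelines in the control arm, not of skipped requests, and goes on to name provider training and steering-committee supervision as countermeasures. Skipped follow-ups are one plausible form of such departure and no more.

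Fourth, the two indexes are meant to be read together, and skipping lowers the first. That is true, but the first index cannot show what share of generated requests was handled.

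**Conclusion.** The point holds in limited form. As written, average handling time is conditional on handling and has no place for requests never handled or still open at withdrawal or trial end. Neglect is unpenalised. If the abandoned requests would have waited longest, the arm's mean is too short and the ranking of arms can reverse.

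Direction and size cannot be determined from the document. Neglect of controls would flatter the control arm; dropped extra requests would flatter the intervention arm. Every handling-time figure above rests on assumed exponential times and assumed shares. Work efficiency is a minor secondary outcome, listed last, and the primary systolic blood pressure analysis is unaffected. The correction is still worth making because it is cheap and the present definition fails for a foreseeable kind of record.

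**What to change.** In Work efficiency of care providers, replace the average of handling times with the following:

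- Include every generated request and analyse time from generation to handling, separately for each follow-up type.
- Censor requests still open at the patient's withdrawal, death or T2. Keep requests that were skipped or overtaken by a later one as unhandled through the window.
- Compare arms on the restricted mean time to handling over a pre-specified window that is the same in both arms. By Table 1, only regular follow-ups arise in both arms, so the between-arm comparison rests on that type.
- Report the proportion of generated requests handled, by arm and type. Even this alone would expose the problem.

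The cost is a few sentences and a short extra analysis. The article says requests are generated and recorded in the system, so no new data should be needed, provided the log keeps unhandled requests; that should be confirmed. The reported time will be longer in an arm that leaves requests open, as it should be. Censoring at withdrawal assumes that leaving is unrelated to how long the open request would have waited, which should be stated.
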